### **6.4.3 Milligram equivalent exposure to BZDs**

Effect of various interventions on milligram diazepam equivalent per day exposure to BZDs has shown mean reductions ranging from 25% to 85%. If clinics are randomly assigned to a treatment group and a control group, with an equal number of patients in both groups, a GEE model with a total sample size of 3000 patients, each measured two times before and after intervention, will have statistical power in the range of 0.678-0.969 to detect differences in means of 0.25 or higher in milligram equivalent exposure when the standard deviation is below 2. Pre-period measurements will include the 12-month period prior to index, and post-period measurements will include the 12 months following index. This assumes that the baseline correlation between observations is 0.2 or higher and that we will observe a 20% attrition rate. Power increases for larger mean difference values and drops significantly at higher standard deviation values.

### **6.4.4 Discontinuation rate of BZDs**

A systematic review of literature has demonstrated discontinuation rates between 27-80% for interventions to reduce exposure to benzodiazepines. If clinics are randomly assigned to a treatment group and a control group, with an equal split between the two groups, a GEE model with a total sample size of 3000 patients, each measured two times before and after intervention, will have statistical power in the range of 0.859-1.000 to detect differences in post-intervention event probabilities in the range of 0.25-0.85. There is significant drop in power for detecting group differences below 0.25. Baseline probabilities in the treatment and control group are assumed to be in the range of 0.010-0.050 and we assumed a 20% attrition rate.

## **6.5 Interim Analysis**

No interim analyses of the study are planned.

## **6.6 Control of Bias**

Both statistical controls and design elements are used to control for bias in the measurement of study outcomes. The longitudinal pre-treatment post-treatment design helps to control for natural rate of deprescribing in a prevalent user population.

## **6.7 Handling of Missing Values**

We will apply no imputation method to this data. All data are observational, and randomization should balance missingness across samples. As such, it is unlikely that missing values will create selection bias. Additionally, our chosen statistical method allows for estimation of longitudinal effects even if patients have a missing outcome value.

# **7 SAFETY MANAGEMENT**

The primary mechanism for safety monitoring will be monthly check-ins by a postdoctoral research fellow who is part of the study team. As a part of monthly check-in calls, the fellow will inquire about any reported adverse effects from opioid and BZD deprescribing, such as increased pain, anxiety and

trouble sleeping. The educational intervention will include instructions for providers to notify clinic staff of any adverse effects, such as withdrawal. Additionally, the instructions will state that the provider should notify the study team directly if any serious adverse events, such as seizures from BZD, occur.

Withdrawal symptoms are a normal and common result of deprescribing. Prescribers of these medicines are familiar with these symptoms, and additional information on withdrawal will also be included in the educational materials. Options for patients who experience adverse effects from deprescribing include contacting the nighttime call service, walk-in clinics, visiting the emergency department, and same-day service at providers' offices. These usual sources of care will be available to assist patients if the need arises.

## **8 DATA COLLECTION AND MANAGEMENT**

Data collection and management of focus group and web-based survey data are described in Section 3. Additionally, data will be held in a password-protected folder on a shared drive accessible to all members of the study team involved with analysis and interpretation of focus group results.

For the cluster-randomized trial, data for the primary and secondary analyses will be gathered from the EHR at baseline and after the 1-year intervention. The primary and secondary outcomes are observational and do not require direct data collection from patients and providers. All information needed for these analyses will be recorded as a part of usual care. Data will be stored on a secure, HIPAA-compliant research workspace managed by Research Computing, a division of UNC Information Technology Services (ITS). The server requires an ONYEN and a two-factor authentication to log on, which is managed by ITS. There are two level of users, Level 1 and Level 2. Level 1 users will have access to all identifiable data, and Level 2 will have access only to coded datasets.

Identifiable data will be collated by the Carolina Data Warehouse for Health (CDWH) and loaded onto the server by a member of the study team, [name], PhD. All data from CDWH will be received as comma-separated values (CSV) files and will be converted into SAS databases when loaded onto the secure server. He will replace any personal identifiers (e.g. medical record number, beneficiary ID number, name, etc.) with a randomly generated patient ID specific to the study. He will load data into a folder accessible to lower-level users who cannot access or view the fully identified files. All users will be limited to members of the study team and will include only those members who need to analyze or interpret data. [name], PhD will lead the analysis, with support by [name], MS and [name], PhD.

[name] will oversee data quality efforts. Data from surveys will be captured and stored to support easy retrieval. Codebooks containing variable names and descriptions will be created for all files. The codebooks will be stored on the same server as the data. Missing responses in surveys will be identified, and consideration will be given as to discarding a partially complete response vs. including items to which a participant responded when data are analyzed. [name] has nearly a decade of experience managing datasets for clinical and observational studies, will lead efforts to clean the EHR data and prepare data for analysis. A record of linkages between EHR datasets will be maintained and kept in the same folder as the codebook. Missing data will be explored, and any missingness that appears unbalanced between the intervention and control clinics will be reported to the study team for consideration. When data are analyzed, [name] will ensure that all coders adhere to the pre-established codebook and expand upon the codebook when new derived variables are added to the database.

Data for the outcomes in Aim 3 will be collected from providers via the web-based survey.

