| Study Duration                                         | Focus groups: two focus groups (120 minutes each)
Web-based survey: 1 survey, given twice: pre-study and post-study
Cluster-randomized trial: 1 year
The entire study is expected to last 4 years                                                                                                                                                                                                                   |
| Study Phases
Screening
Observation | Focus groups: Participants will sign a consent form prior to the start of the focus group session.
Web-based surveys: The surveys will include a written statement stating that their participation in the survey is voluntary and by completing the survey they are consenting to participate.
Cluster-Randomized Trial: Each clinic's 'study champion' will sign a consent form prior to the clinic's participation. |
| Safety Evaluations                                     | The risk from focus groups and web-based surveys is expected to be minimal. To monitor safety from the educational intervention, we                                                                                                                                                                                                                                                                                                               |

---

---

will include specific monitoring criteria in the educational intervention itself (e.g., monthly follow-up with clinic champions about the study), with specific instructions to alert study staff if any adverse effects of deprescribing are observed. Additionally, a study team member will reach out to all intervention clinics monthly to ask about potential safety risks related to deprescribing.

---

---

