## 3.2 Study Duration, Enrollment and Number of Subjects

This study will last for 4 total years. Year 1 will consist of organizing the study team and conducting focus groups. In Year 2, clinics will be randomized, and the educational intervention will be finalized for testing. The cluster-randomized intervention will begin in the 7th month of year 2 and last through the 6th month of year 3. Data analysis will be conducted in the remainder of year 3 and into year 4.

We expect the following number of participants:

- Focus Groups: 12 patients, 12 providers
- Web-based surveys: 120 providers
- Cluster-randomized trial:
  - Number of clinics (intervention & control): 20;
  - Number of patients (intervention and control): 3,000

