### **5 SCREENING AND MONITORING EVALUATIONS AND MEASUREMENTS (how measurements will be made)**

In addition to the focus group instruments and web-based surveys, the development of which are detailed in Section 3, the following outcomes will be used for the cluster-randomized trial.

**The primary outcome for this study is opioid and BZD exposure, as measured by dose and discontinuation rate. A secondary outcome variable is the rate of falls.** We will also evaluate providers' satisfaction with the deprescribing toolkit. For clinicians providing services at an Intervention Group clinic, we will assess three outcome variables that reflect the process of service delivery: (1) whether or not their patients received education on opioids and BZD and their relationship to falls; (2) whether or not the deprescribing toolkit was utilized as part of the deprescribing process; and (3) whether or not HCPs referred to deprescribing toolkit recommendations concerning medication and non-medications to reduce the patient's risk of falls.

➤ **Opioid and BZD Exposure:** The primary outcome of this study will be exposure to opioid and/or BZD. This will be measured in two ways: (1) dose and (2) discontinuation. We will convert all opioid prescriptions to morphine milligram equivalents (MME), and all BZD prescriptions to diazepam milligram equivalents (DME). The method for calculating MME is well-established, and recommended by the CDC for evaluating opioid-related complications. Calculating DME is analogous, and has been used in previous work to evaluate exposure to BZD and has been used previously to evaluate success of discontinuation interventions. For each class of medications, we will calculate milligram equivalents for all observable prescriptions in the 12 months prior to the index and in the 12 months

post-index. To create a more conservative estimate of the impact of the intervention, we will assume that any authorized refills were filled. [DATA SOURCE: Epic EHR]

Discontinuation will be defined as a lack of opioid or BZD prescription from 181 to 360 days after the index. It is acknowledged that the intervention may not have an immediate impact on opioid and BZD discontinuation as prescribers taper patients' doses down, therefore a gap is given to allow for tapering in advance of discontinuation. [DATA SOURCE: Epic EHR]

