### 6.3 Statistical Methods

**Primary Analyses:** We will examine between-group differences in opioid and BZD exposure associated with an increased risk of falls in the intervention and control groups. Analyses will be performed using the following intention-to-treat principle, and index dates for the intervention group will correspond to the date on which they first received any intervention-related clinical activity. Index dates for otherwise eligible patients from the control group will be chosen at random from each patients' set of clinic visits corresponding to an eligible intervention visit during the study period. Our primary hypotheses are:

- Relative to individuals in both control groups, individuals in both intervention groups will experience a significant reduction in the milligram equivalent exposure to opioids and BZDs during the 1-year follow-up period.

- Relative to individuals in both control groups, individuals in both intervention groups will experience a significantly greater discontinuation rate of opioids and BZDs during the follow-up period 181 to 360 days after index.

There are two overlapping groups of patients aged 65+ that will be included in this study: opioid users and BZD users. For each hypothesis, there will be separate models comparing the impact of the program on opioid users and BZD users. Patients who use both will appear in both models. To examine any differential impact of the program among patients who use both classes of medications, a sensitivity analysis will be performed and will include an indicator variable for patients who use both classes.

Generalized estimating equations (GEE, PROC GENMOD) will be used to create longitudinal pre-post model for the milligram equivalent exposure models. An identity link with a normal distribution will be used for milligram equivalent exposure. The functional form of the model is as follows:

$$\text{Eq. 1: } Y = \beta_0 + \beta_1 X_{\text{exp}} + \beta_2 X_{\text{period}} + \beta_3 X_{\text{exp} \times \text{period}} + \beta_n X_n + \epsilon$$

Where  $X_{\text{exp}}$  is the exposure group indicator,  $X_{\text{period}}$  is the pre-post indicator, and  $X_{\text{exp} \times \text{period}}$  is the period-by-treatment interaction indicator and, correspondingly,  $\beta_3$  is the parameter of the difference in outcome by period for the intervention group compared to the control.  $X_n$  represents a vector of covariates.

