## 6.4 Sample Size and Power:

### 6.4.1 Milligram equivalent exposure to opioids

Effect of various interventions on milligram equivalent exposure to opioids has shown mean reductions ranging from 31% to 49%. A GEE model (continuous outcome) with a total sample size of 3000 patients, each measured two times before and after intervention will have statistical power in the range of 0.865-0.999 to detect differences in means of 0.30 or higher in milligram equivalent exposure when the standard deviation is in the range of 1 to 3. Pre-period measurements will include the 12-month period prior to index, and post-period measurements will include the 12 months following index. This assumes that the baseline correlation between observations is 0.2 or higher and a 20% attrition rate will be observed. Another assumption is that we will assign subjects randomly to an intervention group and control group with an equal split between the two groups. Notably, if the standard deviation of observations is above 3.0 or if the attrition rate is greater than 20%, then our statistical power will drop significantly. All calculations were performed using PASS Software.

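### With no last index date and no extraction date, the schedule does not secure the 12-month and day 181–360 outcome windows

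*Protocol*

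**What the plan says.** **Calendar.** The synopsis gives the duration as "Cluster-randomized trial: 1 year" and adds that "The entire study is expected to last 4 years". Section 3.2 starts the intervention in the seventh "month of year 2 and last through the 6 th month of year 3", that is, study months 19 to 30. It continues: "Data analysis will be conducted in the remainder of year 3 and into year 4". No follow-up phase after month 30 is scheduled.

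**Index dates.** These are patient-specific. Under Section 6.3, "index dates for the intervention group will correspond to the date on which they first received any intervention-related clinical activity". A control patient's index is a randomly chosen clinic visit in the study period, taken from visits that correspond to an eligible intervention visit. Neither arm has a last permitted index date.

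**Outcome windows.** Section 5: "Discontinuation will be defined as a lack of opioid or BZD prescription from 181 to 360 days after the index". For dose, Section 6.4.1 says that "post-period measurements will include the 12 months following index". Section 6.3 compares falls over 12 months on each side of index, whereas Section 5 describes the falls period as a year following the intervention.

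**Data.** Section 8: "data for the primary and secondary analyses will be gathered from the EHR at baseline and after the 1-year intervention". Section 6.7 rules out imputation, expects randomization to balance missingness, and relies on the model's tolerance of missing outcome values.

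**The concern.** A patient indexed late in the intervention year needs almost another year of records before any outcome is complete. The calendar puts the start of analysis right after the intervention ends and ties the data pull to nothing later than that.

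The form of the outcomes makes this more than lost follow-up. Discontinuation is the absence of a prescription, so an unobserved stretch of the window looks the same as success unless it is flagged. Dose is built from the prescriptions that can be seen, so a shortened post-period set against a full pre-period looks like a reduction. A fall after the data cut looks like no fall. None of these would appear as a missing value, so neither the model's tolerance of missing outcomes nor the check for unbalanced missingness in Section 8 would necessarily pick them up.

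If both arms were cut equally, the main effect would be to dilute true differences. If they were cut unequally, a difference could appear or vanish because of the data cut alone. Unequal truncation is possible because the arms are indexed by different rules. Both primary outcomes and the falls outcome are exposed.

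**Working it through.** **Inputs from the protocol**
- Intervention: month 7 of year 2 to month 6 of year 3 (Section 3.2).
- Windows: 12 months after index for dose and falls (Sections 6.3, 6.4.1); days 181–360 for discontinuation (Section 5).
- Study length: 48 months (synopsis, Section 3.2).

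**Reproducing the stated duration.** Month 7 of year 2 is study month 12 + 7 = 19, and month 6 of year 3 is 24 + 6 = 30. Months 19 to 30 make 12 months, which agrees with the stated year.

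**When the last window closes.** The last possible index is at the end of month 30, and 30 + 12 = 42, i.e. month 6 of year 4. Day 360 falls about five days earlier. If the falls period in Section 5 is instead read as the calendar year after the intervention, it covers months 31–42 and ends at the same point.

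**Share of windows complete at a given extraction.** Follow-up is the extraction day minus the index day, both counted from the start of the intervention. With extraction *m* months after the start, the extraction day is 30.4375 × *m*. A 12-month window is complete if follow-up is at least 365 days, and the discontinuation window if it is at least 360. No day of the discontinuation window is seen if follow-up is under 181.

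The protocol does not say how index dates spread over the year, so three patterns were assumed over 365.25 days: uniform, and two front-loaded ones (exponential with scale 182 or 90 days, truncated at 12 months). The share indexed by day *x* is:
- uniform: *x*/365.25
- front-loaded, scale *s*: (1 − e^(−x/s)) / (1 − e^(−365.25/s))

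Examples for a complete 12 months, with *x* = extraction day − 365:
- Month 30, uniform: (365.25 − 365)/365.25 = 0.1%.
- Month 36, uniform: (547.875 − 365)/365.25 = 50.1%.
- Month 36, scale 90: (1 − e^(−182.875/90)) / (1 − e^(−365.25/90)) = 88.4%.

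Each cell gives uniform / scale 182 / scale 90:

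| Extraction at end of study month | Complete 12 months | Complete days 181–360 | No day of 181–360 seen |
|---|---|---|---|
| 30 | 0.1 / 0.2 / 0.3% | 1.4 / 3.3 / 5.8% | 49.6 / 26.5 / 11.4% |
| 33 | 25.1 / 45.7 / 65.0% | 26.4 / 47.6 / 67.0% | 24.6 / 9.9 / 3.0% |
| 36 (end of year 3) | 50.1 / 73.2 / 88.4% | 51.4 / 74.4 / 89.1% | none |
| 39 | 75.1 / 89.9 / 96.9% | 76.4 / 90.6 / 97.2% | none |
| 42 | 100% | 100% | none |

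At month 36, then, 12% to 50% still lack a complete 12 months. For scale, the power calculations allow 20% attrition; under uniform indexing the incomplete share is still 25% at month 39.

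**Arm difference, illustration only.** Suppose three visits per patient fall at random over 365 days, intervention patients are indexed at the first and controls at a random one, and data are pulled at month 30. No day of the discontinuation window is seen when index falls later than day 365 − 181 = 184. The shares are (181/365)³ = 12% and 181/365 = 50%. With two visits the first becomes (181/365)² = 25%. The visit counts, their spacing and indexing at the first visit are all assumptions.

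**The case against.** The strongest reply is that the protocol never says data are pulled at month 30. A pull after the intervention has a lower bound but no upper one, analysis is stated to run into year 4, and month 42 lies within that period. Outcomes are routine EHR records that keep accruing and can be extracted retrospectively. Analysis in year 3 could cover the surveys and data preparation. Section 5's falls wording can itself be read as expecting a further year of records. The detailed rule for incomplete windows may sit in an analysis plan that is not shown.

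Much of this stands. A reader might infer that the windows cannot be observed for most patients. That needs an extraction date the protocol does not give, and even at the end of year 3 half or more would be complete under the patterns tried. A reader might also take the 12% versus 50% contrast as a known bias between arms. It is not: the first intervention-related activity need not be the first visit of the year, and the requirement that control visits correspond to an eligible intervention visit may bring the arms' timing closer together.

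What the reply does not remove is the calendar itself, which is protocol content. A one-year trial, an undated pull after that year and an analysis start in month 31 do not fit windows that close as late as month 42, and nothing ties one to the other.

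**Conclusion.** The point holds as a failure to secure the outcome windows, not as proof that they will be missed. The conflict follows from calendar arithmetic and assumes only that index dates may fall throughout the intervention year, which nothing in the protocol prevents.

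The size depends on an extraction date that is not stated. For a pull when the intervention closes, almost no window would be complete under any of the three patterns. For a pull at the end of year 3, the incomplete share depends heavily on how front-loaded indexing is. From month 42 the problem disappears, apart from EHR lag. That truncated windows would be scored as discontinuation, lower dose or no fall is a risk created by how the outcomes are defined; the protocol does not say they would be. Unequal truncation by arm is possible, but its size cannot be determined from the protocol. Because both primary outcomes and falls are exposed and the remedy is simple, it should be settled before outcome data are extracted.

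**What to change.** 1. In Sections 3.2 and 8, set the final outcome extraction at no less than 12 months plus a stated EHR lag after the last index date, which with indexing to month 30 means after month 42. Place the outcome analysis after it.
2. Alternatively, set a last index date early enough for an earlier extraction. For a pull at month 36, indexing would have to close by the end of month 24 (36 − 12), less the EHR lag.
3. State that windows cut short by the extraction date count as incomplete, not as discontinuation, zero exposure or absence of falls. Limit this to administrative truncation, so that patients are not excluded for death or leaving care, which would sit badly with the intention-to-treat statement in Section 6.3.
4. Reconcile Section 3.2 (calendar), Section 5 (exposure and falls periods), Section 6.3 (index dates) and Section 8 (data pulls) so that all use the same windows and dates.

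The cost of the first option is wording and a later outcome analysis: 48 − 42 = 6 months of the study remain, less the lag. The second keeps an earlier analysis but shortens the indexing period and may reduce the number of patients.
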